**Effect of advanced periodontal self-care in patients with early stage periodontal diseases on endothelial function: A randomized controlled trial**

**Funded by:**

Japan Society for the Promotion of Science

SECOM Science and Technology Foundation

PROTOCOL SUMMARY

| Title | Effect of advanced periodontal self-care in patients with early stage periodontal diseases on endothelial function: A randomized controlled trial |
| --- | --- |
| Study Description | To evaluate the effect of periodontal self-care in patients with early stage periodontal diseases on endothelial function, the changes of ACVD-related vascular function markers FMD and serum ADMA level were compared between standard care group and advanced care group. |
| Study Design | Parallel group, 3-month follow-up, open-label, randomized controlled trial. |
| Study Duration | Estimated duration for the main protocol (from start of screening to last subject processed and finishing the study) is approximately 2.5 years |
| Study Center | Department of Translational Research, Tsurumi University School of Dental Medicine, Yokohama, Japan |
| Objectives | Primary Objective: To evaluate the efficacy of advanced periodontal self-care on endothelial function  Secondary Objectives: To evaluate the association between FMD and serum ADMA level |
| Number of Subjects | 110 randomized patients in two arms; advanced self-care in addition to standard care and standard care |
| Inclusion/Exclusion Criteria | Inclusion Criteria   - Male and female, 20-70 years old, in any distribution - Having ≥20 functioning teeth. - Diagnosis of early stage periodontal diseases. - Consent and compliance with all aspects of the study protocol, methods, providing data during follow-up contact.   Exclusion Criteria   - Difficulty in traveling alone to the institution. - Diagnosis of severe periodontal diseases. - Necessity for prosthodontic treatment. - Presence of an untreated carious cavity. - Presence of a partially impacted tooth. - having used systemic antibiotics within the previous 3 months. - Used regular medication for any other chronic disease. - Involvement with any other ongoing studies. |
| Intervention | Test Group: Will receive disinfectant application using custom-fabricated tray in addition to standard care for periodontal diseases  Control Group: Will receive standard care for periodontal diseases |

PROTOCOL SCHEMA

[figure not shown]

SCHEDULE OF ACTIVITIES

|  | **Visit 1** | **Visit 2-1** | **Visit 2-2** | **Visit 3-1** | **Visit 3-2** |
| --- | --- | --- | --- | --- | --- |
| **Procedures** | Screening  Day -60 to -1 | Randomization  Baseline assessment  Day 0 (Control) | Baseline assessment  Day 0 (Test) | Final assessment  Day 90 ± 3 | Custom tray setting for control  (Optional) |
| Informed consent | X |  |  |  |  |
| Demographics | X |  |  |  |  |
| Dental history | X |  |  |  |  |
| Medical history | X |  |  |  |  |
| Concomitant medication review | X | X | X | X | X |
| Randomization | X |  |  |  |  |
| Dental examination ^a^ | X | X | X | X | X |
| FMD measurement |  | X | X | X |  |
| Serum chemistry ^b^ |  | X | X | X |  |
| Blood pressure measurement |  | X | X | X |  |
| Dentition impressions |  | X |  | X |  |
| Administer study intervention |  | X | X |  |  |
| Adverse event review and evaluation | X | X | X | X | X |
| ^a^ bleeding on probing, periodontal pocket depth; ^b^ ADMA, C-reactive protein | | | | | |

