**Randomization**

The eligible patients will be allocated randomly to the test or control group via the envelope method stratified by the smoking habit, which is a common risk factor for ACVD and periodontal diseases.

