**Sample Size Calculations**

The sample size was calculated based on a previous study that a sample size of 90 was needed to detect a 1% difference in FMD (primary outcome) between the two groups, with a standard deviation of the mean difference of 1.67% at a 2-sided α error of 0.05 and 80% power.

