**Statistical Analysis Plan**

Primary Endpoint: FMD.

Secondary Endpoint: Serum ADMA level.

All analyses will be performed using per-protocol population as well as intention-to-treat population.

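### The protocol describes a comparison of changes in FMD after smoking-stratified randomization but states no adjustment; adding baseline FMD and smoking stratum to the primary model would usually gain precision at negligible cost

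*Protocol*

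**What the plan says.** Four places in the protocol bear on this.

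- **Protocol Summary, Study Description.** The between-arm comparison is described in one sentence: "the changes of ACVD-related vascular function markers FMD and serum ADMA level were compared between standard care group and advanced care group". No test, model or covariate is named.
- **Randomization.** Allocation is made "via the envelope method stratified by the smoking habit, which is a common risk factor for ACVD and periodontal diseases".
- **Sample Size Calculations.** The text states that "a sample size of 90 was needed to detect a 1% difference in FMD (primary outcome) between the two groups". The other inputs given there are an SD of 1.67%, a two-sided alpha of 0.05 and power of 80%. There is no term for a covariate or for a baseline correlation.
- **Statistical Analysis Plan section of the protocol.** The endpoint is given only as "Primary Endpoint: FMD", without saying whether this is the Day-90 value or the change. Serum ADMA is the secondary endpoint. The one analysis rule is "All analyses will be performed using per-protocol population as well as intention-to-treat population".

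FMD and ADMA are scheduled at baseline and at Day 90. Smoking habit must be known in order to stratify. Both adjustment variables are therefore already collected.

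**The concern.** Subtracting baseline amounts to fixing its coefficient at 1. When baseline and follow-up are imperfectly correlated, the best-fitting coefficient is below 1 (it equals rho if the two variances are equal). A simple change score then over-corrects: it carries avoidable variance, and it shifts with any chance baseline difference between the arms.

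Smoking raises a related point. Stratifying on a prognostic factor balances the arms on it. An analysis that then leaves the factor out does not credit that balance, and its standard errors are larger than they need be. The protocol's reason for stratifying is that smoking bears on both disease processes under study, which makes it a natural covariate.

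What is at stake is precision and sensitivity to chance imbalance. The validity of the trial is not in question.

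**Working it through.** **1. The protocol's own figure.** Inputs from Sample Size Calculations: difference 1%, SD 1.67%, two-sided alpha 0.05, power 80%.

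- Normal approximation: n per arm = 2 × 1.67² × (1.960 + 0.842)² / 1² ≈ 43.8, so 44 per arm and 88 in total.
- Two-sample t-test: 44.76, so 45 per arm and 90 in total.

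The stated 90 is reproduced by an unadjusted two-sample t-test.

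**2. Variance of the two estimators.** Assume the same SD, s, at baseline and Day 90, with correlation rho.

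- Change score: variance 2s²(1 − rho).
- Adjusted for baseline: variance s²(1 − rho²).
- Ratio of adjusted to change: (1 + rho)/2, which is 0.65, 0.75, 0.85 and 0.95 at rho 0.3, 0.5, 0.7 and 0.9.

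**3. Power.** Read 1.67% as the SD of change. The adjusted SD is then 1.67 × √((1 + rho)/2). With N participants in total and n per arm, the standard error is SD × √(2/n) × √(1 + 2/(N − 5)), on N − 4 degrees of freedom. This charges the adjusted analysis for two covariates and credits it with no gain from smoking. Smoking is taken as two-level.

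Example, rho 0.5 and 45 per arm: SD = 1.67 × √0.75 = 1.446. SE = 1.446 × √(2/45) × √(1 + 2/85) = 0.308. Power on 86 degrees of freedom is 0.894. For the unadjusted change, SE = 1.67 × √(2/45) = 0.352, and power on 88 degrees of freedom is 0.802.

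| Analysis | Power, 45 per arm | Power, 55 per arm | Total N for 80% power |
|---|---|---|---|
| Unadjusted change | 0.802 | 0.875 | 90 |
| Adjusted, rho 0.3 | 0.931 | 0.969 | 62 |
| Adjusted, rho 0.5 | 0.894 | 0.945 | 70 |
| Adjusted, rho 0.7 | 0.853 | 0.917 | 80 |
| Adjusted, rho 0.9 | 0.813 | 0.885 | 88 |
| Adjusted, rho 0.95 | 0.803 | 0.877 | 90 |
| Adjusted, rho 0.98 | 0.797 | 0.872 | 92 |

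**4. Chance imbalance.** If the arms differ by d at baseline, the change-score estimate is shifted by −(1 − rho)d. For a difference of one standard error at 45 per arm, the size of the shift is 1.67 × √((1 − rho)/45). That is 0.21, 0.18 and 0.14 percentage points at rho 0.3, 0.5 and 0.7, or 14% to 21% of the 1-point target. Adjustment for baseline removes it.

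**5. Other reading of the SD.** The protocol calls the 1.67% "with a standard deviation of the mean difference of 1.67"%, which is ambiguous. If it is the SD of Day-90 FMD, the totals for 80% power by the normal approximation, change against adjusted, are 124 against 80 (rho 0.3), 88 against 66 (0.5), 54 against 46 (0.7) and 18 against 18 (0.9). The direction is the same up to 0.7, and the advantage has gone by 0.9.

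**The case against.** The strongest reply is that the protocol fixes no model. The sentence in the Protocol Summary is a brief study description. Model and covariates are commonly left to a separate statistical analysis plan, which is not at hand, so their absence is not a fault in itself. The Goals of the Study, the sample-size text and the endpoint line all refer to FMD without saying change. A sample-size calculation with no covariate term is conservative for a later adjusted analysis and does not show that the analysis will be unadjusted.

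All of this stands. A reader might infer that the plan compares raw changes and ignores the smoking stratification, but the documents do not support that. A comparison of changes can include baseline as a covariate, and it then gives the same treatment effect and standard error as a model of Day-90 FMD. No passage says that smoking will be left out.

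It is also fair to say that:

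- the unadjusted comparison is valid, and on the protocol's own inputs it has 80% power at 90 participants and 87.5% if all 110 are evaluable;
- rho is not in the documents, and the benefit shrinks as rho rises;
- the protocol calls smoking a risk factor for disease and does not say that it predicts FMD once baseline FMD is known, so any extra gain from smoking cannot be computed;
- the adjustment is not wholly free, because it spends two degrees of freedom.

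None of this removes the core point. The one comparison the protocol describes is of changes, its own analysis section adds no adjustment, and a usually more precise method is available from data already collected.

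**Conclusion.** The point holds as a recommendation on efficiency. If changes were compared without adjustment, the result would be valid but, for rho up to about 0.9, less precise than one adjusted for baseline and stratum. The variance reduction from baseline alone is 35%, 25%, 15% and 5% at rho 0.3, 0.5, 0.7 and 0.9. At 90 analysed, power rises from 0.80 to between 0.93 and 0.81 over that range. At 110 it rises from 0.875 to between 0.97 and 0.885. Near rho 0.95 the gain is almost nil, and from 0.98 upwards there is a very small loss.

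These sizes rest on three assumptions: 1.67% is the SD of change, the variances are equal at the two visits, and rho lies in the range shown. They include nothing for smoking.

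A reader might go further and conclude that the planned analysis is wrong or underpowered, or that clinic must also be in the model. The documents support neither. The stated sample size reproduces, and clinic is not a stratification factor, so including it would be a matter of preference.

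**What to change.** In the protocol's Statistical Analysis Plan section, state the primary analysis as a linear model of Day-90 FMD (or, equivalently, of its change) on arm, baseline FMD and smoking stratum. Report the adjusted difference with its 95% CI. Analyse ADMA in the same way with baseline ADMA as the covariate. Reword the Study Description in the Protocol Summary to match. If a separate analysis plan already says this, the protocol need only agree with it.

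The Schedule of Activities must also be reconciled. It marks randomization at Visit 1, where FMD is not measured, yet the Visit 2-1 column header also names randomization, and baseline FMD appears at Visits 2-1 and 2-2. The text should make clear whether baseline FMD precedes allocation in both arms. This matters for a change score as much as for an adjusted model, since both use that measurement.

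The cost is a sentence or two of text and two degrees of freedom (more if smoking has more than two levels). No new data are needed for the adjustment.

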**Reasons for Withdrawal or Termination**

A subject may be discontinued from the study at any time if the subject or the investigators feels that it is not in the subject’s best interest to continue. The following is a list of possible reasons for study treatment discontinuation:

- Screening Failure
- Subject withdrawal of consent
- Subject is not compliant with study procedures
- Adverse Event that in the opinion of the Investigator would be in the best interest of the subject to discontinue study participation
- Protocol violation requiring discontinuation
- Lost to follow-up
- Contract diseases that make it difficult to continue research
- Subject death

All subjects are free to withdraw from participation at any time, for any reason, specified or unspecified, and without prejudice. Reasonable attempts will be made by the Investigator to provide a reason for subject withdrawals. The reason for the subject’s withdrawal from the study will be specified in the subject’s source documents and the Case Report Form. If a subject is withdrawn from treatment due to an adverse event), the subject will be followed and treated by the Investigator until the abnormal parameter or symptom has resolved or stabilized. The Investigator must make every effort to contact subjects who are lost to follow-up.

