**Methods and Study Schedule**

Subjects eligible for the study will review and undergo informed consent. Once consented, subjects will be randomly assigned on a 1:1 basis to undergo:

- Control Group: Current standard care for periodontal diseases
- Test Group: Application of disinfectant with a custom-fabricated prescription tray in addition to standard care

*Visit for Screening (-60 to -1 days from Day 0)*

The following procedures will be performed at the Screening visit:

- Review the study with the subject and obtain written informed consent
- Assign the subject a unique screening/enrollment number
- Record demographics (age, gender)
- Review and record medical history, surgical history, and medication history to determine eligibility based on inclusion/exclusion criteria
- Document all current medications, including medications over-the-counter and herbal medications

*Visit for Treatment (Day 0)*

After baseline measurements, the following techniques will be used according to the arm the patient is randomized to:

Control Group:

The 55 subjects will undergo typical standard care for periodontal diseases.

Treatment Group:

The 55 subjects will undergo application of disinfectant with a custom-fabricated prescription tray in addition to standard care.

*Visit for endpoint measurements (Day 90)*

The following procedures will be performed at the visit for endpoint measurements:

- Assess for adverse events
- Document all current medications, including medications over-the-counter and herbal medications

*Unscheduled Visit*

The following procedures will be performed if the subject presents to the clinic at any other time point not specified above:

- Assess for adverse events
- Document all current medications, including medications over-the-counter and herbal medications

*Early Termination*

All subjects have the right to withdraw from study participation at any time during the study. If, for whatever reason, a subject withdraws from the study, an Early Termination visit will be performed.

The following procedures will be performed (if agreed upon by the subject) at the Early Termination visit:

- Assess for adverse events
- Document all current medications, including medications over-the-counter and herbal medications

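### The schedule gives two different times for randomization and puts Day 0 at different visits in the two arms, so in this open-label trial at least the test arm's baseline FMD is taken after allocation.

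*Protocol*

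**What the plan says.** **Timing of randomization.** The row in the Schedule of Activities reads "Randomization | X", with its only mark under Visit 1. That is the screening visit, which Methods and Study Schedule heads "Visit for Screening (-60 to -1 days from Day 0". The column header of Visit 2-1 in the same table also names randomization. Methods and Study Schedule states "Once consented, subjects will be randomly assigned on a 1:1 basis". The Randomization section says that patients are "allocated randomly to the test or control group via the envelope method stratified by the smoking habit" and gives no time.

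**Timing of baseline.** The headers place Day 0 at Visit 2-1 for control and at Visit 2-2 for test ("Day 0 (Control) | Baseline assessment"). The FMD row is "FMD measurement | | X | X | X": nothing at Visit 1, then Visits 2-1, 2-2 and 3-1. Serum chemistry (ADMA, C-reactive protein) and blood pressure follow the same pattern. Impressions are "Dentition impressions | | X | | X", so at 2-1 and 3-1 but not at 2-2. The interval between 2-1 and 2-2 is not given. Methods and Study Schedule describes one undivided treatment visit on Day 0 and puts baseline before treatment, but does not say that baseline comes before allocation.

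**Blinding and endpoint.** The design is open-label, and no FMD assessor unaware of the arm is described. The Protocol Summary compares changes in FMD and ADMA. The Statistical Analysis Plan section names the primary endpoint simply as FMD.

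**The concern.** A baseline serves as an unbiased reference only if it cannot depend on the arm. Here the person measuring FMD and the participant may both know the arm when at least the test arm's baseline is taken. That value also comes at a separately labelled visit, probably after an additional attendance. Operator expectation, familiarity with the procedure, or a change in oral hygiene after learning the arm could each move it.

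The primary comparison depends on this value, whether as the starting point of a change or as a covariate. Intention-to-treat analysis does not repair a baseline that was measured differently by arm, and a clean baseline cannot be recovered once participants have started. Visit order and the definition of Day 0 are protocol content, so this is not a detail left to a separate statistical analysis plan.

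**Working it through.** **1. Order of events under each reading of the protocol**

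| Source for time of allocation | Allocation | Control baseline (2-1) | Test baseline (2-2) |
|---|---|---|---|
| Schedule, Randomization row | Visit 1, Day -60 to -1 | after allocation | after allocation |
| Methods and Study Schedule | after consent (consent is at Visit 1) | after allocation | after allocation |
| Schedule, header of Visit 2-1 | Visit 2-1 | same visit; order within the visit not fixed, though randomization is listed first | after allocation |

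The three sources do not agree on the time, but in all of them the test arm's labelled baseline follows allocation. In two of the three, every baseline value in both arms does.

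**2. Who attends Visit 2-1**

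The table does not say. Impressions are needed for a custom tray and are marked at 2-1 and not at 2-2. An optional tray for controls follows at Visit 3-2, after impressions at 3-1. The likely reading, which is an inference, is that test participants attend 2-1 for impressions and return at 2-2. If so, the table leaves open whether they have FMD twice and which value is their baseline.

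**3. The plan's own sample-size figure**

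Inputs from Sample Size Calculations: difference 1.0, SD 1.67, two-sided α 0.05, power 80%. The two-sample t-test needs 44.76 per arm, so 45 per arm and 90 in total. The stated 90 reproduces, and this point does not affect it. The same SD is used below.

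**4. What a baseline shift would do (illustration; the shift sizes b are assumed)**

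Suppose there is no true effect, and allocation moves one arm's mean baseline by b without moving Day 90. In an unadjusted comparison of changes the bias equals b in size.

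- Standard error = 1.67 × √(2/n): 0.318 at 55 per arm (the planned number), 0.352 at 45 per arm.
- Noncentrality δ = b / SE. Type I error = P(|T| > critical value), where T is noncentral t with 2n − 2 degrees of freedom.
- At 55 per arm, critical value 1.982: b = 0.2 gives δ = 0.63; b = 0.3 gives δ = 0.94; b = 0.5 gives δ = 1.57.

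| Assumed shift b (FMD points) | Type I error, 55 per arm | Type I error, 45 per arm |
|---|---|---|
| 0 | 5.0% | 5.0% |
| 0.2 | 9.5% | 8.7% |
| 0.3 | 15.4% | 13.5% |
| 0.5 | 34.3% | 29.0% |

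**5. With baseline adjustment**

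The bias becomes slope × b. With an assumed slope of 0.5 and, for simplicity, the same SD, a shift of 0.2 leaves a bias of 0.1 and a type I error of about 6.1% at 55 per arm. A shift of 0.5 leaves 0.25 and about 12%. Adjustment shrinks the problem without removing it.

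**The case against.** The strongest reply is that the layout is deliberate: each arm's Day 0 is the day its care starts, and the paired FMD and intervention marks mean one per arm. On that reading the 90 days run from the start of care in both arms, which is a real advantage. It explains the two columns. It does not explain why allocation has to be known before the test arm's baseline, and it does not resolve the conflict between the Randomization row and the header. The protocol schema is not reproduced in the available text and may clarify the flow, but it could not make the row and the header agree.

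A second reply is that the size of the harm is hypothetical. This stands. The documents give neither size nor direction for any shift. The bias equals the shift only in an unadjusted comparison of changes, and only if the shift is absent at Day 90. An influence acting at both visits would partly cancel. The protocol does not fix the analysis model, so adjustment may be planned.

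Three stronger readings are tempting, and the documents do not support them:

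- **Randomization before eligibility is checked.** A reader might infer this from "Once consented, subjects will be randomly assigned on a 1:1 basis". But that paragraph opens with subjects who are already eligible, and the Randomization section likewise allocates eligible patients. The wording is at most loose.
- **Exclusions after randomization.** A reader might infer these because "Screening Failure" is among the reasons for discontinuation. It is one item in a generic list, and nothing says that such subjects have been randomized.
- **Test-arm care before baseline.** The intervention is marked at both 2-1 and 2-2, so the table allows this reading. Methods and Study Schedule puts care after baseline, so it is a discrepancy to reconcile and not a stated plan.

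**Conclusion.** The point holds in a limited form. The protocol gives inconsistent times for randomization. On each of them the test arm's labelled baseline follows allocation and is assigned to a different visit from the control arm's, in an open-label trial with no blinded FMD assessor described. Baseline FMD and ADMA can therefore be influenced by allocation. That they will be, and by how much, cannot be shown from the documents.

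The type I error of 9.5% for a 0.2-point shift and 15.4% for 0.3 points rests on four things: the assumed shifts, the protocol's SD of 1.67, 55 per arm, and an unadjusted change score with a shift gone by Day 90. A shift of 0.2 is one fifth of the 1.0-point target difference, so a small disturbance would matter. It is worth correcting because the route for bias is avoidable and the remedy uses a visit already in the schedule.

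**What to change.** - In every participant, confirm eligibility and complete the baseline dental examination, FMD, serum chemistry and blood pressure at Visit 2-1. Open the allocation envelope only then.
- Move the Randomization mark from Visit 1 to Visit 2-1, and amend the sentence in Methods and Study Schedule that randomizes on consent, so that it requires confirmed eligibility and completed baseline measurements.
- Use the Visit 2-1 values as the single baseline in both arms, and remove the separate test-arm baseline at Visit 2-2.
- State from which event Day 90 is counted in each arm.
- The sponsor should reconcile the intervention marks at Visits 2-1 and 2-2 with the statement in Methods and Study Schedule that care follows baseline.

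**Cost.** A short amendment to the schedule and the related text, with no added visit. The real trade-off is that the test arm's baseline will precede tray delivery by the tray-making interval, whose length the protocol does not give. Counting Day 90 from baseline puts that interval inside the test arm's follow-up; counting it from tray delivery makes the time from baseline to endpoint differ between arms. The protocol should state its choice and the reason. If a later test-arm baseline has to stay, an FMD assessor unaware of allocation is a lighter partial safeguard. It would not remove the effect of the extra visit or of the participant knowing the arm.
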